### Further information on health economics’ analysis

We will undertake a comprehensive cost-utility analysis with both NHS and societal perspectives. We will make an assessment and valuation of costs (direct and indirect costs) and benefits (QALY gains) as a result of the 3-month smoking cessation intervention. The major cost drivers will be patient’s use of NHS and private health services, the patient’s time and their travel costs and intervention delivery costs. To achieve this we will calculate:Cost of intervention (e.g. staff time, resources and equipment used and room costs).Costs to participants (being based on the distance to SHU or smoking cessation clinics and travel costs, time taken-off from work to attend sessions and any additional liquids or NRT-based medication bought by participants).Difference in resource use between groups (elicited from the resource use diary).Differences in patient experiences and health related outcomes between intervention and control groups (assessed via the EQ5D-5 L questionnaire, which using the standardised general population based tariff, would allow us to have its scores converted into QALYs and then undertake a comparison between study groups).Incremental Cost-Effectiveness Ratio (ICER) (derived from relating differences in costs to benefits between study groups during the 6-month period).

We will use standard published sources for unit costs where available and supplement this with local sources if required. We will use imputation methods for missing data, analysis of uncertainty and non-normal distributions: i.e. standard statistical analysis of costs will be performed to test for statistical significance of results, while bootstrapping would be performed to estimate the CI of average interventional costs.

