### Follow-up visits

*VISIT 2:* Within 3 days of “quit date”, vascular assessment of micro- and macro-vascular function *(see Outcomes).*

*VISIT 3:* 3 months past quit date, scheduled to coincide with current local NHS practice, all baseline measurements will be repeated, compliance will be measured in the resource use diaries as per NHS behavioural support strategy [23].

*VISIT 4:* 6 months past quit date, baseline measurements and compliance assessment will be repeated.

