### Measures

*Baseline (Visit 1)*
Demographic data, including age and sex.Clinical history (including smoking history), previous operations, comorbidities, current medications, height, weight and blood pressure.Fägerstrom Test of Cigarette Dependence FTND; [24].EQ5D-5 L to support Health Economics’ assessment; [25].Q-Risk to assess risk of CVD; [26].Short Form (SF)- International Physical Activity Questionnaire (IPAQ) to assess physical activity; [27].Macro-vascular function [22],Upper-body micro-vascular function [28],“Finger prick” test to calculate the total cholesterol (TC) over High Density lipoprotein (HDL) ratio [29].Carbon monoxide (CO) breath levels [30].

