Microvascular assessments using Laser Doppler Fluximetry and Iontophoresis as described in the literature; [28] will be performed at all study visits, in a temperature-controlled room (22–24 °C) in the ventral surface of the experimental (right) arm extended to the side at heart level. These will be used as indicators of the changes occurring in the endothelial –dependent and –independent vasodilatory function. Heart rate (Sports Tester, Polar, Finland) and blood pressure (left arm; Dinamap Dash 2500, GE Healthcare, USA) will be monitored at 5-min intervals throughout the protocol. The two drug delivery electrodes ((PF383; Perimed AB, Jarfalla, Sweden) will be positioned over healthy looking skin, approximately 4 cm apart with one containing 100 μL of 1% acetylcholine (ACh; Miochol-E, Novartis, Stein) and the other 100 μl of 1% sodium nitroprusside (SNP; Nitroprussiat, Rottapharm). A battery-powered iontophoresis controller (PeriIont PF382b; Perimed AB) will be used to provide the charge needed for ACh and SNP delivery. A 4 min stable recording of baseline flux will be followed by administration of the two agents according to the following protocol: 0.2 mA for 10 s (i.e., 2 mC), 0.2 mA for 15 s (i.e., 3 mC), 0.2 mA for 20 s (i.e., 4 mC), and 0.3 mA for 20 s (i.e., 6 mC), happening between 4-min intervals. To obtain an index of skin blood flow, cutaneous red cell flux will be measured by placing an iontophoresis laser-Doppler probe (PF481–1; Perimed AB), connected to a laser Doppler fluxmeter (PF5001; Perimed AB).b)Micro-vascular function at 6 months (measured as described for a).c)Smoking status at 3 and 6 months, self-reported and biochemically validated by exhaled air measurement of <10 ppm Carbon monoxide in line with the Russell Standard [30].d)change in CVD risk at 3 and 6 months compared with baseline, measured using Q-riske)Health Economic effects (assessed using EQ5D-L and a resource use diary) at 6 months. The EQ-5D is a generic measure of health status, where health is characterized on five dimensions (mobility, self-care, ability to undertake usual activities, pain, anxiety/depression).The EQ-5D has been validated in the UK and has been used in other clinical trials i.e. [31].f)Total cholesterol (TC) and High Density lipoprotein (HDL) via finger prick blood sample at 3 and 6 months; HDL is negatively affected by smoking [29], and improvements in the TC/ HDL ratio can be demonstrated 3 weeks after quitting [32].

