### Data analysis

SPSS 21.0 will be used to enter quantitative data and cleaning the data and to carry out missing values imputation and statistical analysis. Data will be reported and presented according to the revised CONSORT statement [33].

Analyses will be performed on an intention-to-treat basis. Double data entry will be implemented to to promote data quality. Where applicable, tests will be two-tailed with statistical significance being set at *p* ≤ 0.05. Baseline demographic (i.e. age, gender, HSI), physical measurements (e.g. weight, height, BMI), carbon monoxide and nicotine dependence levels, as well as Q-Risk, SF-IPAQ and EQ5D-L will be assessed for comparability between groups.

An Analysis of Variance (ANOVA) will be used to compare mean macro- and micro-vascular function between groups. A 95% confidence interval (CI) for the mean difference in these parameters between the three groups will also be calculated. In the event of differences between groups with respect to baseline measurements, multiple regression will be used to adjust the treatment effect for these variables, with the stratification covariates being included in the analysis. The ordinary least squares adjusted regression coefficient estimate for the e-cigarette groups’ parameter, along with its 95% CI, will then be reported. Secondary outcomes at 6-months will be analysed similarly. For repeated assessments at baseline, and at all follow-up sessions a summary measure (e.g. “Area under the Curve”) will be calculated for each participant.

Finally, a further subgroup analysis of those who ceased smoking completely will be undertaken and results will be compared amongst the three groups.

For qualitative data analysis, audio recording of the interviews will be made, transcribed verbatim, and the five stages of framework analysis of familiarisation, identifying a thematic framework, indexing, charting, and mapping will be followed [34, 35].

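### Adjustment of the QALY comparison for baseline EQ-5D is at best conditional on an undefined baseline imbalance; it should be made in every case

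*Protocol article*

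**What the plan says.** **Collection.** The Measures section lists the instrument at Visit 1 ("EQ5D-5 L to support Health Economics"). Under Follow-up visits, at Visit 3 (3 months) "all baseline measurements will be repeated", and the Visit 4 entry reads "6 months past quit date, baseline measurements and compliance assessment will be repeated". Utility is therefore available at 0, 3 and 6 months.

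**Status.** Outcome measures lists among the secondary outcomes "Health Economic effects (assessed using EQ5D-L and a resource use diary) at 6 months".

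**Adjustment rule.** Data analysis includes EQ-5D in the baseline check ("as well as Q-Risk, SF-IPAQ and EQ5D-L will be assessed for comparability between groups") and then states: "In the event of differences between groups with respect to baseline measurements, multiple regression will be used to adjust the treatment effect for these variables". The stratification covariates enter that model. The same paragraph applies the approach to secondary outcomes at 6 months.

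**QALY comparison.** The health economics section says the scores will be "converted into QALYs and then undertake a comparison between study groups", and derives the ICER from cost and benefit differences over 6 months. It mentions imputation, significance tests of costs and bootstrapping. It neither names a covariate nor refers back to the rule in Data analysis.

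**The concern.** Baseline utility predicts later utility. If QALYs are the area under the utility curve, it is also the first point of that area. Those are the reasons to adjust for it, and they hold whether or not the arms happen to differ at Visit 1.

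The written rule makes adjustment depend on an observed difference instead. It does not say whether a difference is judged by a test, by its size or by eye, nor whether across three arms or pair by pair. It therefore leaves two weaknesses:

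- Imbalance short of the trigger stays in the QALY difference and hence in the denominator of the ICER.
- Whether the economic model is adjusted at all depends on the data.

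At stake is the precision of the incremental QALYs, and their conditional accuracy given the imbalance that actually occurred. The protocol lists a cost-utility analysis among its specific objectives.

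**Working it through.** The article gives no utility SD, no correlation between visits and no expected QALY effect, so there is no QALY figure of its own to reproduce.

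**Inputs**
- Visits at 0, 3 and 6 months, and a 6-month horizon: from the article.
- 66 per arm: the article's number before the dropout allowance, taken here as the number with EQ-5D data.
- Assumed: utility SD 0.2 (range 0.1 to 0.25); the same correlation r between any two visits, 0.3 to 0.7; a trapezoid QALY; adjustment triggered when the baseline difference between two arms has p≤0.05.

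**Step 1: carry-over of a baseline difference D**

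QALY = 0.125·U0 + 0.25·U3 + 0.125·U6. Given D at baseline, U3 and U6 are each expected to differ by r·D, so the unadjusted QALY difference moves by (0.125 + 0.375r)·D:
- r = 0.3: 0.2375·D
- r = 0.5: 0.3125·D
- r = 0.7: 0.3875·D

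**Step 2: size of chance imbalance**

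SE of the baseline difference = SD·√(2/n) = 0.2·√(2/66) = 0.0348 (0.017 to 0.044 for SD 0.1 to 0.25). An imbalance of one SE moves the QALY difference by 0.0083, 0.0109 and 0.0135 for r = 0.3, 0.5 and 0.7. The largest imbalance that escapes the assumed trigger is about 1.96 × 0.0348 = 0.068. It moves the QALY difference by 0.016, 0.021 and 0.026.

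**Step 3: three policies compared**

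- Variance of the unadjusted QALY difference: V = SD²·(2/n)·(0.09375 + 0.15625r).
- Part due to baseline imbalance: B = SD²·(2/n)·(0.125 + 0.375r)².
- Always adjusting leaves V − B.
- Adjusting only when p≤0.05 leaves (V − B) + 0.72·B. The factor is the share of variance retained by a standard normal within ±1.96: 0.95 − 2 × 1.96 × 0.0584 = 0.72.

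A simulation with estimated coefficients (5,000 trials, no treatment effect) gave these SDs of the QALY difference. The closed form agrees to within about 0.0002.

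| r | B/V | Never adjusted | Adjusted if p≤0.05 | Always adjusted | Always vs conditional |
|---|---|---|---|---|---|
| 0.3 | 0.40 | 0.0130 | 0.0124 | 0.0102 | about 18% lower |
| 0.5 | 0.57 | 0.0145 | 0.0133 | 0.0097 | about 27% lower |
| 0.7 | 0.74 | 0.0159 | 0.0141 | 0.0080 | about 43% lower |

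At r = 0.5 the conditional rule recovers (0.0145 − 0.0133)/(0.0145 − 0.0097) = 0.0012/0.0048, a quarter of the available reduction; at r = 0.3 and 0.7 it recovers slightly less. In the closed form the percentages do not depend on SD or n, because both cancel. They depend on r and on the trigger.

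**Step 4: the definition of QALY gain**

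The article speaks of QALY gains without defining them. If change from baseline is meant (the QALY minus 0.5·U0), the shift becomes −(0.375 − 0.375r)·D, that is −0.26·D to −0.11·D, with the opposite sign. With U0 in the regression both definitions give the same arm difference, because subtracting 0.5·U0 changes only the coefficient of U0.

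**The case against.** The strongest reply is that the plan does provide for adjustment. Data analysis checks baseline EQ-5D, adjusts by regression where differences appear and treats 6-month secondary outcomes in the same way; Outcome measures makes the health economic effects one of those outcomes. A reader of the economics section alone might infer that QALYs will be compared unadjusted. The documents do not support that. The quoted words say neither adjusted nor unadjusted, and a journal article may leave the covariates of an economic model to a fuller document. Silence there would not be a finding.

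This disposes of the flat claim but not of the point. What remains is a stated rule: adjustment depends on an observed and undefined difference. Even read as generously as possible, that is the most the article offers for the QALY comparison.

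Three further limits stand:
- The carry-over is partial, not one for one.
- Under randomisation, chance imbalance does not bias the comparison on average.
- The fair comparator for the gain is the conditional rule, not a comparison that is never adjusted, so the larger saving against the unadjusted column should not be claimed.

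**Conclusion.** The point holds in this form: baseline EQ-5D adjustment of the QALY difference is at best conditional on an undefined imbalance, and the economics section does not carry even that rule into the QALY comparison or the ICER.

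The cost is lost precision, with the SD of the QALY difference about 18% to 43% lower under unconditional adjustment, plus conditional error when a moderate imbalance goes uncorrected. These figures rest on the assumed correlations, the trapezoid and the p≤0.05 trigger. The absolute values also rest on the assumed SD of 0.2 and on 66 per arm. A looser trigger would narrow the gap and a stricter one would widen it.

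A reader might go further and infer a biased ICER, or a QALY effect swamped or reversed by imbalance. The documents give no expected QALY effect against which to judge that, and randomisation rules out systematic bias from this source. The primary FMD analysis is not touched by this point. Severity is low to moderate: a free improvement.

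**What to change.** Add to the health economics section that incremental QALYs will be estimated by regressing each participant's 6-month QALY on arm, baseline EQ-5D-5L utility and the stratification factors (gender and pack-years), fitted whatever the observed baseline imbalance, and that the adjusted difference will be used in the ICER. In the same place, define how the QALY is calculated from the 0-, 3- and 6-month scores.

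The cost is a sentence or two. Baseline utility is already collected and multiple regression is already among the planned methods, so no visit, measurement or participant is added.

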### Safety monitoring

Study investigators will be responsible for recording adverse events and for determining the seriousness, severity, causality and expectedness of any such events.

The study Primary Investigator will monitor patient safety within the trial and will be responsible for reviewing any adverse events occurring as part of the trial in collaboration with a delegated clinician and confirming that they have been appropriately classified.

Participants will be asked to contact the study team to inform them about adverse events if and when they occur. Study investigators will also question participants about the occurrence of adverse events during each participant study visit.

We will record all serious adverse events, as well as all non-serious adverse events that are deemed to be related to participation in the research, during the period between provision of informed consent through to 12 months after randomisation.

Serious adverse events are defined as any untoward medical occurrence that results in one of the following criteria:Results in death,Is life threatening (i.e. event in which patient is at risk of death at the time of the event occurring),Requires unplanned or prolonged hospitalisation (unplanned refers to emergency hospitalisations. Prolonged hospitalisation is deemed to be where a patient’s stay is longer than expected (e.g. patient is operated on as day case but remains in hospital overnight)Results in persistent or significant disability or incapacity

A non-serious event in the context of this trial will be any untoward medical occurrence to the participant that is related to the participants’ involvement in the study, but does not fulfil any of the serious adverse event criteria.

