Electronic (or “e-“) cigarettes or vaping devices uses battery power to disperse a solution that usually contains propylene glycol or glycerine, water, flavouring and nicotine [13]. They have become the most popular smoking cessation aid in England [14], while evidence suggests that they are efficacious as smoking cessation aids [15]. However, data on their effects on cardiovascular function is limited i.e. [16] and there is a lack of consensus within the smoking cessation community as to their potential impact: consequently, further research has been requested by the European Parliament [17], the British Medical Association [18], regulatory agencies, clinicians and researchers Lancet; [19], BMC Public Health; [20]. As e-cigarettes are not solely nicotine-based products, existing research exploring the effects of nicotine on the cardio-vasculature (e.g. coronary and peripheral vasoconstriction, intravascular inflammation and deregulation of cardiac autonomic function as well as inhibition of microcirculation; [21]) provides only limited information. Evidence is needed to inform the general public, smokers and policy-makers.

This study aims to assess effects on cardiovascular physiology in smokers making a quit attempt using e-cigarettes (either nicotine-free or nicotine-inclusive) in comparison with smokers making a quit attempt with prescription NRT.

The specific objectives of the study include:The comparison of the effects that nicotine-inclusive e-cigarettes (Group A), nicotine-free e-cigarettes (Group B) and NRT (Group C) have on cardiovascular physiology both acutely (e.g. within 3 days of “quit date”) and in the medium term (6 months following “quit date”), by measuring: a) endothelial-dependent, macro-vascular function and b) endothelial-dependent, micro-vascular function. The inclusion of Group B (nicotine-free e-cigarettes), will allow us to determine whether the e-cigarette vapour constituents have a distinguishable effect on cardio-vasculature against a nicotine-inclusive e-cigarette (Group A).Comparison of the effect of the different treatments on cardiovascular disease risk.An in-depth exploration of the participants’ study experience in a sub-sample of participants.Defining facilitators and barriers of smoking cessation in each of the 3 groups.Assessing the economic cost implications that the approaches have on the NHS and the study participants, by undertaking a Health Economics’ Cost Utility Analysis.

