### Study setting

All assessments will be undertaken at the Centre for Sport and Exercise Science (CSES) of Sheffield Hallam University. Behaviour support will be primarily provided in Sheffield Hallam University premises in Collegiate Crescent or City campuses to cover the widest possible Sheffield population, with both locations being easily reached from all Sheffield areas. This setting was chosen to ensure appropriate data collection, to assess its acceptance by participants and monitor their physical and emotional wellbeing, as the university has extensive experience of delivering lifestyle interventions to clinical populations (e.g. cancer, heart failure, aortic aneurysm, chronic venous insufficiency and intermittent claudication). Group C will be referred to NHS smoking cessation clinics in Sheffield (*Yorkshire Smokefree Sheffield*), provided by South West Yorkshire Partnership NHS Foundation Trust.

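### Non-serious adverse events are recorded only if deemed related to the research, by investigators whose blinding is not stated, so events judged unrelated cannot be reviewed or compared by arm

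*Protocol article*

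**What the plan says.** All of the rules are in the protocol article, Safety monitoring.

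- Serious events carry no relatedness condition: "We will record all serious adverse events". The four criteria are death, threat to life, unplanned or prolonged hospitalisation, and persistent or significant disability.
- Non-serious events carry one. The same sentence continues "as well as all non-serious adverse events that are deemed to be related to participation in the research".
- The definition builds the condition in again. A non-serious event is "any untoward medical occurrence to the participant that is related to the participants’ involvement in the study" that meets none of the serious criteria.
- On who decides: "Study investigators will be responsible for recording adverse events and for determining the seriousness, severity, causality and expectedness of any such events". The Primary Investigator then reviews events, "in collaboration with a delegated clinician and confirming that they have been appropriately classified".
- Participants are asked to report events as they occur and are questioned about them at each study visit.

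The section on randomisation and blinding names outcome assessors, the statistician and the health economist as blinded. It does not mention those who judge causality.

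**The concern.** Causality is normally a property recorded about an event. Here, for non-serious events, it decides whether there is a record at all. Two consequences follow.

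The first is loss. An event judged unrelated leaves no adverse-event entry, so a wrong judgement cannot be found or corrected. This matters most where knowledge is thin. The Abstract calls the information on cardiovascular effects of e-cigarettes limited and contradictory, and an unexpected effect is one that an investigator may well call unrelated. The Background lists nicotine effects that include "coronary and peripheral vasoconstriction, intravascular inflammation and deregulation of cardiac autonomic function as well as inhibition of microcirculation", yet related symptoms that do not lead to emergency admission would usually meet none of the serious criteria.

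The second is possible distortion between arms. The test is relatedness to taking part in the research, and the arms differ in how they meet the research. Groups A and B receive devices and liquid from the trial, whereas "Group C will be referred to NHS smoking cessation clinics in Sheffield". The same symptom might be credited to the trial in one arm and to ordinary care in another. If the person judging knows that Group B is nicotine-free, attribution could also differ between A and B, the contrast for which Group B was included.

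An analysis plan cannot repair either problem, because it cannot analyse events that were not collected.

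**Working it through.** The protocol gives no figure on this point, so there is none to reproduce. The check is a reading of the rules, followed by a small illustration.

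**Step 1: does an unrelated non-serious event have a place in the record?** Only two categories are to be recorded.

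| Event | Meets a serious criterion | Deemed related | Recorded |
|---|---|---|---|
| Serious, related | yes | yes | yes |
| Serious, unrelated | yes | no | yes |
| Non-serious, related | no | yes | yes |
| Non-serious, unrelated | no | no | no |

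The last row is excluded by the recording rule and again by the definition, so this is not a slip in one sentence.

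**Step 2: can the second review recover it?** The Primary Investigator and delegated clinician confirm the classification of events. On the wording, the non-serious events that reach them have already been judged related. They can downgrade a wrong call of related, but they never see a wrong call of unrelated.

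**Step 3: when does the filter bias a comparison?** Let t be the true proportion of participants with a non-serious event, the same in both arms, and let q be the probability that such an event is deemed related.

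- Recorded proportion = t × q.
- Recorded ratio, A to C = (t × qA) / (t × qC) = qA / qC. The true proportion cancels.

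Inputs: n = 86 per group (Sample size section). The values t = 0.40 and the q values are assumptions; the protocol gives neither.

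| qA | qC | Recorded in A | Recorded in C | Ratio |
|---|---|---|---|---|
| 0.5 | 0.5 | 86 × 0.20 = 17.2 | 86 × 0.20 = 17.2 | 1.00 |
| 0.6 | 0.4 | 86 × 0.24 = 20.6 | 86 × 0.16 = 13.8 | 1.50 |
| 0.7 | 0.3 | 86 × 0.28 = 24.1 | 86 × 0.12 = 10.3 | 2.33 |

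The true count is 86 × 0.40 = 34.4 per arm throughout. With equal attribution of 0.5, half the participants with events go unrecorded in each arm but the ratio is unbiased. With unequal attribution a ratio above 1 appears although the arms do not differ. The ratios are the same at t = 0.20 and t = 0.60.

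**The case against.** The case for leaving the rule alone has several parts.

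*The safety log is not an outcome.* Adverse events are not among the primary or secondary outcomes, and Data analysis describes no comparison of them. Serious events are fully recorded. This stands and limits the importance of the point. It does not remove it: the article commits to CONSORT reporting and aims to inform the public and policy, and any harms table by arm would carry the filter.

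*Other data would pick up some events.* Blood pressure is measured at baseline, repeated at 3 and 6 months, and monitored during the microvascular protocol at all visits. Comorbidities and current medications are among the baseline measures that are repeated. The resource use diary collects GP visits, tests, medications and hospital days linked to smoking cessation or smoking-related disease. This also stands in part. Raised blood pressure would not be missed, and some other events would leave a trace. None of these sources is an adverse-event record with date, severity and causality.

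*NRT is an allocated treatment.* The trial refers Group C and reimburses its prescription charges, and all groups are questioned at the same visits. A reaction to NRT is not excluded by the text. This is fair: unequal attribution is possible, not shown.

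Three stronger readings are tempting and are not supported. A reader might infer that the judges are unblinded; the article does not say either way. A reader might infer that events are filtered by opinion about the product; the written criterion is participation in the research. A reader might infer that recorded counts must differ between arms; the rule is worded identically for all three, and counts differ systematically only if attribution does. For the same reason, a probability that a spurious difference reaches significance would rest on assumed rates and on a test that the protocol does not plan.

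**Conclusion.** The point holds as a defect in what is collected. The exclusion of non-serious events judged unrelated is explicit, stated twice, and cannot be undone after data collection. That conclusion depends on no assumption about blinding or attribution.

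Distortion between arms is a conditional risk. It needs attribution that differs by arm, and its size is then the ratio of the attribution probabilities: 1.5 at 0.6 against 0.4, and 2.33 at 0.7 against 0.3, with no true difference. These values illustrate the mechanism and are not estimates for this trial.

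The scope is limited to non-serious events. The primary outcome, flow-mediated dilatation at 6 months, is untouched. The change is worth making because it is cheap and the lost information is not recoverable; it is not a condition for the validity of the main result.

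**What to change.** Replace the recording rule and the matching definition as follows.

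- Record all adverse events reported at or between study visits, in all three groups, whatever their judged relatedness. Define a non-serious event only by the absence of the serious criteria.
- Enter relatedness to the allocated product (e-cigarette, e-liquid or NRT) as a separate field.
- Have relatedness judged by someone blind to arm where existing staff allow, and state in the protocol whether that person knows the allocation.
- Report all-cause events by arm first and related events second.

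If workload is a concern, apply this at least to all cardiovascular and respiratory events.

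The cost is a change of wording in the protocol and the case report form. No extra contact is needed, because participants are already questioned at every visit. The downside is more minor events to enter for 258 participants.

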### Eligibility

*Inclusion Criteria*
Age > 18 years of either sex,Smokers (at least 10 cigarettes/ day for the past year),Willing (by declaration) to attempt quit smoking by using the NHS services or e-cigarettes.

*Exclusion Criteria*
Inability to walk,Recent (within 6 months) cardiovascular disease event (e.g. stroke, myocardial infarction) or cardiac surgery,Insulin-controlled diabetes mellitus or with coexisting skin conditions, leg ulcers, vasculitis or deep venous occlusion (as these may affect their cardiovascular function),Pregnancy,Requiring major surgery during the course of the study),Contraindications /unsuitability for NRT,Current daily use of e-cigarettes,Currently undertaking a cessation attempt supported by a smoking cessation clinic,Unable to give informed consent.

*Withdrawal*s.

Participants will be considered as withdrawn from the trial if they request to leave the trial, if they are lost to follow-up, or if they die before completing the 12-month follow-up.

Participants will be considered as withdrawals from the allocated treatment if they no longer use the electronic cigarette, or if they no longer receive NRT-based, smoking cessation therapy. Withdrawals from the trial and from the allocated treatment will be included in the analysis by intention-to-treat. Standard care for participants who decide to withdraw from the study will not be affected.

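### The closed list of serious adverse events counts only emergency or prolonged admissions, so a new cardiovascular event managed electively or as an outpatient is not serious and, if also judged unrelated, is not recorded as an adverse event

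*Protocol article*

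**What the plan says.** The definition in the Safety monitoring section is closed: "Serious adverse events are defined as any untoward medical occurrence that results in one of the following criteria". Four criteria follow.

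- Death.
- A threat to life, explained as an "event in which patient is at risk of death at the time of the event occurring".
- Admission: "Requires unplanned or prolonged hospitalisation (unplanned refers to emergency hospitalisations". Prolonged is explained as a case where the "stay is longer than expected (e.g. patient is operated on as day case but remains in hospital overnight".
- Disability: "Results in persistent or significant disability or incapacity". The list ends here.

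All serious events are to be recorded, "as well as all non-serious adverse events that are deemed to be related to participation in the research", from consent to 12 months after randomisation. The section's own definition of a non-serious event also requires a link to taking part in the study. Study investigators decide seriousness and causality. The principal investigator reviews the classification with a delegated clinician.

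The Eligibility section excludes smokers with a "Recent (within 6 months) cardiovascular disease event (e.g. stroke, myocardial infarction) or cardiac surgery". It also excludes anyone who will need major surgery while the study runs.

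**The concern.** Seriousness decides whether an event is kept regardless of opinion or kept only if someone thinks the study caused it. Two features make that boundary narrow. Unplanned is equated with emergency, so an admission arranged after consent for a newly found condition does not count unless the stay overruns. There is also no criterion for an event that matters medically but meets none of the other three tests.

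The trial compares the cardiovascular effects of two kinds of e-cigarette and nicotine replacement in smokers. Only recent cardiovascular disease is excluded, so smokers with older disease can enter. If a new cardiovascular diagnosis or procedure falls outside the list, its presence in the safety record depends on one causality judgement. The article states blinding for outcome assessors, the statistician and the health economist. It does not state it for whoever makes that judgement.

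**Working it through.** No arithmetic applies: the point depends on wording, not on alpha, power or sample size. The check is to apply the definition and the recording rule to concrete cases.

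**Step 1: which events are serious, and what happens if they are judged unrelated.**

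| Event after consent | Criterion met | Serious? | Recorded as an adverse event if judged unrelated? |
|---|---|---|---|
| Fatal, life-threatening or disabling cardiovascular event, with or without admission | Death, threat to life or disability | Yes | Yes |
| Emergency admission for a cardiovascular event | Admission (unplanned) | Yes | Yes |
| Planned admission for newly found heart disease, stay longer than expected | Admission (prolonged) | Yes | Yes |
| Planned admission for newly found heart disease, stay of expected length, not life-threatening or disabling | None | No | No |
| New cardiovascular event managed as an outpatient, not life-threatening or disabling | None | No | No |

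In the last two rows the event is recorded if it is judged related, but as non-serious. If it is judged unrelated it falls into neither class, because the definition of a non-serious event itself requires relatedness.

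**Step 2: separate the two conditions.** Loss from the adverse-event record needs both: the event is outside the list, and it is judged unrelated. Removing the relatedness condition alone would get the event recorded, but still as non-serious. Only a change to the list alters the classification.

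**Step 3: set this beside the Eligibility section.** Known need for major surgery during the study is an exclusion. A planned major operation during follow-up is therefore likely to be for something that arose, worsened or was diagnosed after consent, which is what a safety record should hold. The same section names cardiac surgery beside stroke and myocardial infarction as a reason not to enrol. It is an eligibility rule and not a ranking of seriousness, but it shows that the authors regard such procedures as relevant to this population.

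**Step 4: look for other places where the event might appear.**

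- The resource use diary counts hospital days for smoking-related disease and some health-care visits, for the economic analysis. It would count a planned stay. Its hospital-day count would not show an event managed without admission.
- The Follow-up visits section repeats the baseline measurements at 3 and 6 months. According to the Measures section these include clinical history, earlier operations, comorbidities and current medication.
- Investigators ask about adverse events at each visit, but what is then recorded follows the rule in step 1.

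The diary and the repeated history may hold traces of such events. Neither is stated to feed safety review, and the last listed visit is 6 months after the quit date, while the recording window runs to 12 months after randomisation.

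**The case against.** The strongest reply is that little is lost. Deaths, life-threatening events, emergency admissions and disabling events are all serious as the plan stands, and that would take in most acute infarctions and strokes. What remains is elective admissions of expected length and milder outpatient events, and the exclusion for major surgery narrows this further. Even these are recorded when judged related, and the diary or the repeated history may show some of the rest. The definition is explicit, is the same in all three groups and is reviewed with a clinician. The trial's outcomes are physiological, and clinical events are not among them.

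All of this stands, and it limits what can be claimed. A reader might infer any of the following, and the documents support none of them.

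- *That the definition alone removes events from the record.* It does so only together with a judgement of unrelatedness.
- *That the cardiovascular events bearing most on the trial's question are lost.* The acute events named in the exclusion criteria would mostly be captured.
- *That the safety comparison will favour e-cigarettes.* The same rule applies to every group, the article describes no table of serious events by group, and nothing in the definition points in one direction.
- *That a rate of missed events can be given.* The documents contain no figure for it.

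The reply does not remove the gap itself. The rule is stated in full in the article, so it is not a detail left to a document that is not shown. The other sources are not described as safety data.

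**Conclusion.** The concern holds in a limited form. Under the stated definition, a post-consent cardiovascular event that is managed by a planned admission of expected length or without admission, and that is neither life-threatening nor disabling, is not serious. If it is also judged unrelated, it is not recorded as an adverse event.

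The size is modest and cannot be put as a number from the documents. The primary analysis and the sample size are untouched. The conclusion assumes that the list and the recording rule are applied as the article words them, and that the diary and the repeated history do not pass information to safety review, since no such link is stated. It is a cheap improvement that should be made, not a flaw that undermines the trial.

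**What to change.** Change the Safety monitoring section in three places.

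1. Define an unplanned admission as any admission not already scheduled at consent. This brings in a planned admission for a condition that arose or worsened afterwards.
2. Add a criterion for a new cardiovascular event or procedure of the kind named in the exclusion criteria, and for any other event that the delegated clinician judges medically important.
3. State that events meeting the new criterion are recorded regardless of causality, as other serious events already are, and are reported by group.

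These changes concern how events are classified and recorded, not how participants are treated. The cost is a small change of protocol wording, a revised adverse-event form and a few more serious-event forms at a single centre. No visit or procedure is added.
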